SI are temporarily relieved and stabilized through acute cannabis use (i.e., negative reinforcement).

*Hypothesis 1.1:* Negative mood will predict subsequent same-day cannabis use events as well as greater self-reported motivation to use cannabis for mood improvement (EMA Phase 1; Baseline as Usual).

*Hypothesis 1.2:* Negative mood and SI reported within one hour following cannabis use will be lower in intensity and less variable than mood and SI reported during same-day random-prompt EMA reports occurring ≥1 hours since last cannabis use (EMA Phase 1; Baseline as Usual).

*Hypothesis 1.3 (exploratory):* There will be within-subject correlates (e.g., concurrent other substance use, social context of use) and between-subject factors (e.g., cannabis use and depression severity, history of suicidal behavior) that moderate relationships between acute cannabis use and mood and SI.

**Aim 2:** To test if negative mood and SI decrease in overall (mean) levels and variability after cannabis

wash-out.

*Hypothesis 2.1:* Among CB-Abst but not CB-Mon, negative mood and SI reported during random prompt EMA reports will intensify and become more variable throughout the first week of sustained cannabis withdrawal (EMA Phase 2; Randomized Withdrawal) compared to random, non-use events during baseline cannabis use as usual (EMA Phase 1; Baseline as Usual).

*Hypothesis 2.2:* Negative mood and SI reported during EMA random prompts after 8 weeks of abstinence (EMA Phase 3; Randomized Sustained Abstinence) will be lower in intensity and variability than negative mood and SI reported during EMA random prompts occurring during random, non-use events during baseline cannabis use as usual (EMA Phase 1; Baseline as Usual) and withdrawal (EMA phase 2; Randomized Withdrawal). There will be no difference in mood or SI intensity or variability across the 3 EMA phases in CB-Mon.

1. **General Description of Study Design**

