We will conduct a 10-week, multi-method, randomized study, and will recruit 200 school-based adolescents, ages 12-18 years, with daily or near daily cannabis use and current depressive symptoms. The study design is nearly identical to that used in another IRB approved protocol aimed at pilot data collection for the current protocol (#2021P002416), apart from minor modifications to the study population. Participants will complete 2 weeks of real-time EMA during baseline cannabis use (EMA Phase 1; Baseline Use as Usual) to quantify the temporal relationship between cannabis use and mood and SI, and the within- (e.g., concurrent other substance use, social context of use) and between-subject factors (e.g., average severity of cannabis use, depression and SI) that may moderate these linkages. To determine how depression and SI change across short- and longer-term cannabis withdrawal, participants will then be randomized to 8 weeks of monitoring (CB-Mon) or incentivized abstinence via contingency management (CB-Abst). A key aspect of the approach is that the 8-week period is long enough to observe true changes due to cannabis discontinuation, separate from effects of withdrawal and residual cannabinoid exposure that generally subside in 4 weeks. Both groups will complete 1 week of EMA in weeks 1 (EMA Phase 2; Randomized Withdrawal) and 8 (EMA Phase 3; Randomized Sustained Abstinence) of the randomized study period. During all 3 EMA phases, participants will receive 7-9 random, time-stamped prompts per day to ascertain mood and SI in the absence of acute cannabis use, proximal but prior to cannabis use, and during or shortly after cannabis use.

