**Questionnaires:** Surveys will be administered via REDCap, a HIPAA compliant, web-based application hosted by Partners HealthCare designed to support data capture for research studies (http://rc.partners.org/edcredcap), at in-person visits (or virtually via MGB-approved video conference platforms like Microsoft Teams or zoom; V1-12). Construct areas queried include, for example: demographics; cannabis use of family cannabis withdrawal; current and past use of other substance of abuse (e.g., tobacco, alcohol); family rules about substance use; parental messages about substance use; quality of family communication; peer support; social integration; exposure to risky peer networks; self-esteem; coping; depressive, anxiety, and ADHD symptoms; delinquent behaviors; temperament; suicidal ideation; sleeping habits. To enhance reproducibility, measures were drawn from the PhenX Toolkit when available (Hamilton et al., 2011).

**Toxicology:** At all study visits, participants will provide a urine sample, which will be used to qualitatively screen for cannabis use as well as other substances of misuse and quantitatively screen for amount of THC metabolites in urine.

For visits conducted virtually (via MGB-approved video conference platforms like Microsoft Teams or zoom), participants will be given or mailed a qualitative testing and shipping kit. Participants will be guided through the steps of testing the urine sample collected at each visit and will be instructed on how to package the sample for shipment.

**Ecological Momentary Assessment (conducted between V1-V2, V2-V5 and V11-V12):** At baseline, participants will be guided through installing the EMA platform (MetricWire) on their iOS or Android smartphone. Support for app installation and EMA training will be provided throughout the study as needed by phone and via tutorial materials. Participants will be told that surveys will commence the next day and that they should use the app throughout the next 2 weeks in the same way as trained at baseline. During the EMA phases, participants will complete random prompts via MetricWire using a data sampling scheme similar to that used in prior studies (Shiffman et al., 2020). Participants will never be asked to complete >9 random EMA surveys/day. To enhance compliance, participants will be paid a $100 compliance bonus at the end of each EMA phase if ≥80% of random prompts are completed.

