**Remuneration**

Participants may be paid between study visits for their participation. The level of compensation is deemed appropriate given the time commitment. Reloadable cards will be managed by Advarra Participant Payments. Advarra Participant Payments is an MGH-approved, secure, web-based platform that facilitates clinical trial and study-related payments onto prepaid reloadable Visa cards. Participants will be informed of Advarra policy during the consent process. After agreeing to participate in the study, participants will also be asked to sign a “Advarra Participant Payment Card Acknowledgement of Receipt” form to certify their understanding of Advarra Participant Payment policies. The form will require participants to print and sign their name and provide their social security number. If the participant is under 18 years old, then parent/guardian information including date of birth, social security number, and address will be collected. Advarra acknowledgment forms will be stored in a locked study cabinet. Given that the scientific objective of this study necessitates implementation of a robust contingency management protocol which requires immediate payment following verification of cannabis abstinence, the primary payment delivery method will be Advarra. If a participant is under the age of 18 and does not have a parent that is willing to provide a social security number, they may be paid via MGB-issued check. Social security numbers will be stored and protected on the MGB-approved, secure REDCap server. Participants will be compensated for attendance of in-person visits, abstinence (if randomized to CB-Abst), plus a compliance bonus at the end of each EMA phase if ≥80% of random prompts are completed. Cannabis abstinence will be indexed by self-reported non-use and, given cannabis’ long half-life, by progressively decreasing quantitative levels of 11-nor-delta-9-THC-9-carboxylic acid (THCCOOH), the primary cannabis metabolite, in urine. Laboratory processing of cannabis metabolites will be conducted at Dominion Diagnostics.

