**Termination of Participation**

Participants will be terminated from this study if they fail to comply with study procedures or if in the opinion of the principal investigator, can no longer safely participate.

1. **Risks and Discomforts**

**Potential risks in the study are considered minimal and include:** Psychosocial, Social and Legal Risks: There are no uncommon psychological, social, or legal risks associated with participation in this study. Periods of voluntary cannabis abstinence are not uncommon for adolescent users as they often take breaks for participation in sports, family vacations, etc. There is a slight risk that the questionnaires and interviews may contribute to temporary discomfort when participants are asked about distressing symptoms (e.g., suicidal thoughts). Notably, prior research has shown that answering questions about suicidal thoughts and actions does not increase psychological distress or increase one’s suicidal thoughts/behaviors (Reynolds et al., 2006). Nevertheless, a study staff member will monitor the EMA responses and in the event of significantly worsening depressive symptoms, suicidal thoughts, or behaviors (described in detail below), will alert a clinically trained staff member who will follow-up within 24 hours. A doctoral level clinician, including PI [name], will be on call should they be needed.

**Fitbit Risks:** Fitbits used for sleep and activity data pose minimal risk and do not alter the current level of risk for the main study. A small portion of people either find the device uncomfortable or have reactions to the device or band. Alternate material Fitbit bands will be ordered as needed.

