**Potential Benefits to Society**

Information developed from this study may help researchers in the future. The expected scientific yield of the project is substantial. There is much to be learned from the project. Findings have the potential to have measurable implications on policy, prevention, and treatment efforts. The greatest benefit will be to future cohorts of adolescents who will benefit from what is learned from this research project.

The risks associated with this study are minimal and reasonable, particularly in light of the fact that significant knowledge will be gained.

1. **Statistical Analysis**

**Data preparation.** Six negative affect measures will be defined via composite averages and individual scores using EMA items: 1) the average over 5 items assessing depleted mood (scores for feeling Sad, Self-hatred, Numb, Hopeless, and Fatigued), 2) the average over 2 items assessing negative cognitive impacts (scores for feeling Disinterested and Inattentive), 3) the average over 3 items assessing negative activation (scores for feeling Agitated, Irritated, and Anxious), 4) the average over 3 items assessing passive suicidal ideation (scores for Thoughts about death, Wishing suffering could be over, and Better off as dead), 5) the individual item for suicidal urges, and 6) the individual item for non-suicidal self-injury urges. All items will be measured on a 0 (No, not at all) – 100 (Yes, very much) scale. Acute cannabis use will be defined as a binary indicator variable (1 = self-reported use in the hour preceding the current random prompt, 0 = no use in the last hour).Additionally, whether cannabis was used in the last hour to improve negative mood will be assessed on a 0 (No cannabis use) and 1 (No, not at all) – 100 (Yes, very much) scale.

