**Protocol non-adherence.** Analyses involving phase 1 and/or phase 2 of EMA data collection, will only consider CB-Abst participants who have biochemically-validated CB abstinence for two months because the goal is to study the effect of abstinence on change in mood and SI. If fewer than expected CB-Abst abstain from CB use for the full two months, we will form Helmert contrasts: those in CB-Mon (a), CB-Abst who do not abstain (b), and CB-Abst who abstain (c). The 1^st^ Helmert contrast will compare a to b+c and will be the intent to treat comparison. The 2^nd^ contrast will compare b to c, which corresponds to the post hoc sensitivity analysis of interest. Similar considerations will be made if participants in CB-Mon incidentally discontinue CB use during the study.

**Power analysis and justification of recruitment targets for the confirmatory cohort.** The R package ‘EMAtools’ (version 0.1.3; Kleiman, 2017) was used to determine the power for the proposed analyses. Preliminary analyses from the exploratory study found effect size estimates for significant effects ranged from 0.19 to 0.44, and that 77% of participants completed all phases of the study, completing on average 76% of all prompts. Estimates of the power were therefore computed to detect a weak effect (a Cohen’s d of .2) based on linear multi-level models using the nesting structure for the proposed EMA analyses and an intra-class correlation of .09. Table 1 shows the breakdown of estimates power based on the hypothesis being tested under two scenarios: 1) an ideal scenario with the full proposed number of participants and responses, and 2) a realistic scenario where 77% of participants complete 76% of entries.

Table 1: Power estimates by hypothesis and attrition scenario (ideal versus worse-case)

| Hypothesis | N (%) for sample size | N (%) of completed entries | Power |
| --- | --- | --- | --- |
| 1.1 - 1.2 | 200 (100%) | 112 (100%) | 99% |
|  | 154 (77%) | 85 (76%) | 93% |
| 2.1 - 2.2 | 200 (100%) | 224 (100%) | 99% |
|  | 154 (77%) | 170 (76%) | 94% |

1. **Monitoring and Quality Assurance**

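### The protocol gives two different entry rules for the week-1 withdrawal contrast (H2.1), and one of them makes entry depend on abstinence in weeks 2 to 8

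*Protocol*

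**What the plan says.** Hypothesis 2.1 (Specific Aims and Objectives) is that in CB-Abst, but not CB-Mon, negative mood and SI "will intensify and become more variable throughout the first week of sustained cannabis withdrawal", compared with baseline use. The General Description of Study Design sets the timing: "Both groups will complete 1 week of EMA in weeks 1 (EMA Phase 2; Randomized Withdrawal) and 8". Under Assessment Techniques, EMA is "conducted between V1-V2, V2-V5 and V11-V12". In the schedule V2 to V5 are days 14, 16, 19 and 21, and V12 is day 70.

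Three parts of the Statistical Analysis section bear on who enters H2.1:

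- **Data analysis, Aim 2.** CB-Abst data are admitted only where abstinence is confirmed, with phases 2 and 3 named. It is not said whether each phase is judged on its own or both must be met.
- **Protocol non-adherence.** Any analysis using phase 1, phase 2 or both "will only consider CB-Abst participants who have biochemically-validated CB abstinence for two months". If abstinence falls short of expectation, Helmert contrasts are formed from CB-Mon (a), CB-Abst non-abstainers (b) and CB-Abst abstainers (c). The first, a against b+c, is named as the intent-to-treat comparison; the second is b against c. CB-Mon receives similar treatment only for members who happen to stop using.
- **Missing Data.** If methods disagree, CB-Abst participants lost to follow-up are taken to have resumed use.

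On measurement, "At all study visits, participants will provide a urine sample" (Toxicology). Abstinence is indexed by self-reported non-use and "by progressively decreasing quantitative levels of 11-nor-delta-9-THC-9-carboxylic acid" (Remuneration). Under Termination of Participation, "Participants will be terminated from this study if they fail to comply with study procedures".

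**The concern.** H2.1 is a week-1 question, and its outcome is complete at V5. A participant who is abstinent through V5 and relapses in week 6 has supplied a full week of EMA under withdrawal, which is what H2.1 asks for. The two-month rule removes that participant because of something that happened later, and it applies to CB-Abst alone. CB-Mon has no completion condition.

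Conditioning a contrast on events after its outcome can select on that outcome. The protocol's own Hypothesis 1.1 is that negative mood precedes cannabis use. If so, adolescents whose mood worsens most in week 1 may be likelier to return to use and drop out of the analysis. H2.1 would then be estimated in those who tolerated withdrawal best, although it is the trial's test of whether withdrawal worsens mood and SI.

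The Aim 2 wording offers a milder reading that keeps the week-1 data. The two paragraphs can therefore lead two analysts to different H2.1 populations.

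**Working it through.** **1. Does the two-month rule reach H2.1?** H2.1 uses phases 1 and 2, and the rule covers both. Its scope looks like a slip, since taken literally it would also restrict Aim 1, which uses only phase 1, when everyone may use cannabis. If phases 2 and 3 were meant, phase 2 is still covered. Either way the rule applies to H2.1.

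**2. How much later follow-up does entry depend on?**

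- After the H2.1 window: day 70 − day 21 = 49 days.
- Randomised period: day 70 − day 14 = 56 days. Share: 49/56 = 87.5%.
- Later urine tests: V6 to V12 (days 28, 35, 42, 49, 56, 63, 70) = 7.

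**3. The plan's own figure.** Table 1 gives H2.1–2.2 power of 99% (200 participants, 224 entries) and 94% (154 participants, 170 entries) at d = 0.2 and ICC 0.09. A design-effect approximation, effective N = N·n/[1 + (n−1)·ICC], with two-sided alpha 0.05 assumed, gives:

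- 200 × 224/21.07 = 2126, power 99.6%, which agrees with 99%.
- 154 × 170/16.21 = 1615, power 98.0%, not 94%. Applying 77% to N a second time gives 94.1%.

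The point does not rest on this figure. What matters is that 154 = 200 × 0.77 allows for non-completion only, with nothing taken off for completers who do not abstain.

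**4. Illustration (assumed inputs).** Let p be the share of week-1-abstinent CB-Abst participants who later fail the two-month rule. Let g be the extra week-1 worsening of those lost over those kept, in points on the 0–100 item scale. The protocol gives neither.

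- Mean: full = (1−p)·kept + p·lost, so full − kept = p·g.
- Standard error of the CB-Abst change: ratio 1/√(1−p).
- Standard error of the difference from CB-Mon, with w week-1 abstainers and m in CB-Mon: ratio √{[1/(w(1−p)) + 1/m] / [1/w + 1/m]}.

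| | p = 20% | p = 40% | p = 60% |
|---|---|---|---|
| Understatement, g = 0 | 0 | 0 | 0 |
| Understatement, g = 2 | 0.4 | 0.8 | 1.2 |
| Understatement, g = 5 | 1.0 | 2.0 | 3.0 |
| SE ratio, CB-Abst change | 1.118 | 1.291 | 1.581 |
| SE ratio, difference (w = m = 100) | 1.061 | 1.155 | 1.323 |
| SE ratio, difference (w = 50, m = 100) | 1.080 | 1.202 | 1.414 |

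The ratios assume the same person-level variance of change in both arms and among those kept. Selection related to the outcome would alter the variance among those kept. As a guide to p, an assumed weekly loss of 2%, 5% or 10% over seven weeks keeps 0.98⁷ = 87%, 0.95⁷ = 70% or 0.90⁷ = 48%.

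**5. Rough power under the two-month rule.** Take 77 CB-Abst completers, an assumed share of them abstinent for two months, 77 in CB-Mon, and 21 days × 8 prompts × 76% = 128 entries each. The approximation of step 3, with unequal arms, gives 77%, 90%, 95% and 97% at 30%, 50%, 70% and 90% abstinent. With a further factor of 0.76, which brings the full-retention figure to about the stated 94%, these become 66%, 81%, 88% and 92%.

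**The case against.** **The Aim 2 paragraph may govern.** It is the specific plan for H2.1, and read phase by phase it keeps the week-1 data. This stands as a reason not to say that data will be discarded. It does not settle the matter, because the same sentence can equally mean abstinence in both phases and the other paragraph states the two-month condition outright.

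**One group of sustained abstainers is a coherent target.** Aim 2 describes a rise followed by a fall, fitted in one model over phases 1 to 3, and following the same people through both has merit. If they are the intended population, p·g is a difference between two populations and not a bias. That is fair, and it supports keeping this set as a secondary analysis. It does not justify making it the only source of a week-1 estimate.

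**The Helmert fallback.** A reader might infer that the protocol has no intent-to-treat comparison for H2.1. It has one: a against b+c brings back all of CB-Abst, and it is likeliest to be used when loss is large. The limits are that it depends on missing an expectation the protocol does not state, and that b against c still classes a week-1 abstainer who relapses later as a non-abstainer for a week-1 outcome.

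**The size is assumed.** This stands. Precision suffers little unless abstinence is low, when the fallback probably applies.

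**Conclusion.** The protocol does not fix one H2.1 population, and its more explicit rule conditions a week-1 contrast on weeks 2 to 8 in one arm. Under that rule, valid EMA from week-1 abstainers who are lost later is dropped. The conflict and the conditioning follow from the text. The consequence depends on which reading is applied.

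A reader might infer that H2.1 is biased towards no withdrawal effect. The documents do not support that. No abstinence, relapse or termination rate is given, nothing shows that those lost worsened more, and with g = 0 there is no bias, only lost precision. The 0.4 to 3.0 point shifts and the 6% to 32% rise in standard error (difference between arms, w = m = 100) are illustrations under equal person-level variance. They are not converted to Table 1's d, because the variance of person-level change is not given. The point should be corrected before analysis; confidence in its practical size is moderate.

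**What to change.** State one rule in both the Aim 2 and the Protocol non-adherence paragraphs:

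- **H2.1:** CB-Abst participants with self-reported non-use from V2 to V5, and THCCOOH falling from the day-14 level across days 16, 19 and 21, contribute their phase 1 and phase 2 EMA whatever happens later. Day 14 can serve only as the reference level, because V2 follows two weeks of usual use.
- **H2.2:** the two-month rule governs CB-Abst phase 3 data.
- **Scope:** correct the phases named in the Protocol non-adherence paragraph so that Aim 1 is not restricted.
- **Sensitivity analysis:** report the two-month sustained-abstainer set, so that one group is still followed through the rise and the fall.

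The single phase 1–3 model can stay, with phase 3 data absent for those lost later. The cost is wording and one added analysis; the urine tests are already scheduled. The downsides are that H2.1 and H2.2 then use different CB-Abst sets, that week-1 abstinence rests on three follow-up tests in seven days plus self-report, and that H2.1 still conditions on week-1 abstinence, so it is not intent-to-treat.

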**Treatment Assignment and/or Randomization**

If participants meet eligibility criteria and a signed consent form has been received from a parent/guardian, they may be contacted and scheduled for a baseline session. For participants aged 18 years, baseline sessions may be scheduled prior to obtaining consent (as consent will be obtained at baseline prior to administering any study procedures). For all participants, a member of the study team will discuss the consent/assent form with the participant, provide answers to any questions, and, if the participant is interested, a licensed clinician will obtain informed consent/assent. The participant will then be given a signed copy of the consent/assent form.

Once enrolled and after the baseline phase (EMA Phase 1; Baseline as Usual), participants will be scheduled for randomization, which will employ a 2-arm, within-subject, parallel group design to examine effects of short- and longer-term withdrawal across 8 weeks of cannabis abstinence on depression and SI. Participants will be randomized to 8 weeks of abstinence with contingency management (CB-Abst: n=100) or non-contingent monitoring with no abstinence requirement (CB-Mon: n=100) using a 1:1 ratio in blocks of 6. A subset of study staff who will administer surveys and questionnaires querying about mood and suicidality will be blind to group assignment. Randomization will be based on a computerized scheme developed by the study statistician. Randomization will be stratified by age (<=14 years old vs >=15 years old), sex (male vs female), and depression severity (mild/moderate vs. Moderately severe/severe). A key aspect of the approach is that the 8-week period is long enough to observe true changes due to cannabis discontinuation, separate from effects of cannabis withdrawal and residual cannabinoid exposure. Groups will complete 1-week of EMA in weeks 1 (EMA Phase 2; Randomized Withdrawal) and 8 (EMA Phase 3; Randomized Sustained Abstinence) of the randomized study period.

Individuals randomized to monitoring who incidentally stop using cannabis, or express an interest in discontinuing cannabis, will not be removed from the study. If desired, these individuals will be provided with substance use resources at the time of interest in cessation.

1. **STUDY PROCEDURES**

Study procedures are nearly identical to those used in IRB approved pilot protocol (#2021P002416).

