**Data analysis.**

**Aim 1: To test if negative mood and SI are temporarily relieved and stabilized through acute cannabis use (i.e., negative reinforcement cycle).** We will only use phase 1 data, the 2-week baseline period in which all participants may use cannabis. *Hypothesis 1.1:* We hypothesize that negative affect measures for a) the current random prompt, and b) the prior random prompt (a lag-1 term) will predict 1) greater cannabis use independent of motivating reason (i.e., lower probability for the zero component of the model), and 2) higher scores for motivated cannabis use to improve negative mood. Negative affect measures will therefore be converted to z-scores for this analysis and included as predictors for both the zero and non-zero components of the model. *Hypothesis 1.2:* We hypothesize that the binary indicator for cannabis use in the last hour will predict lower, less variable scores for the negative affect measures. Therefore, the binary use indicator will be included as a predictor for the beta regression residual variance term as well. *Hypothesis 1.3 (exploratory):* There will be within-subject correlates (e.g., concurrent other substance use, social context of use) and between-subject factors (e.g., cannabis use and depression severity, history of suicidal behavior) that moderate relationships between acute cannabis use and negative affect.

**Aim 2: To test if negative mood and SI initially increase with the start of abstinence and then decrease in both mean levels and variability after cannabis wash-out.** We will use phase 1 – 3 data, including predictors for a) group differences (CB-Abst vs. CB-Mon), b) differences by phase (phase 3 vs. phase 1 and phase 2 vs. phase 1), and c) terms for the group by phase interactions. All terms will be included as predictors for the beta regression residual variance term as well. We will only include data for the CB-Abst group with confirmed abstinence for phases 2 – 3. *Hypothesis 2.1:* We hypothesize that CB-Abst will show higher mean negative affect scores and greater variability during phase 2 compared to phase 1, while CB-Mon will show no differences between phases. *Hypothesis 2.2:* We hypothesize that CB-Abst will show lower mean negative affect scores and less variability during phase 3 compared to phase 1, while CB-Mon will show no differences between phases.

**Exploratory analyses:** To further assess heterogeneity in suicidal ideation, we will conduct a set of

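### Table 1's reduced-scenario power is misstated: the Aim 1 row uses an all-phase completion rate for a phase 1 analysis, and both reduced rows appear to use a design effect for more entries than they list; both errors are conservative

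*Protocol*

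**What the plan says.** The paragraph on power and recruitment targets (protocol, Statistical Analysis) names the tool: "The R package ‘EMAtools’ (version 0.1.3; Kleiman, 2017) was used to determine the power for the proposed analyses". Its inputs are a Cohen's d of 0.2, "an intra-class correlation of .09", and the pilot experience that "77% of participants completed all phases of the study", with an average of 76% of prompts answered. The reduced case is described as "a realistic scenario where 77% of participants complete 76% of entries", while the title of Table 1 calls it a worse case. The table gives:

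| Hypotheses | N | Entries per person | Power |
|---|---|---|---|
| 1.1-1.2 | 200 | 112 | 99% |
| 1.1-1.2 | 154 (77%) | 85 (76%) | 93% |
| 2.1-2.2 | 200 | 224 | 99% |
| 2.1-2.2 | 154 (77%) | 170 (76%) | 94% |

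For Aim 1, the Data analysis section says: "We will only use phase 1 data, the 2-week baseline period in which all participants may use cannabis". The randomisation section fixes the order of events: "Once enrolled and after the baseline phase (EMA Phase 1; Baseline as Usual), participants will be scheduled for randomization". The paragraph on protocol non-adherence adds that analyses involving phase 1 and/or phase 2 take CB-Abst participants only if they have two months of biochemically validated abstinence.

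**The concern.** The 77% measures retention to the end of the study. It is a suitable input for Aim 2, which needs all three phases. It does not suit Aim 1, because a participant who leaves during the eight randomised weeks has already supplied the phase 1 data. The reduced N for H1.1-1.2 is therefore not the sample expected for that analysis.

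The power figures raise a second question. Going from 200 × 112 to 154 × 85 lowers power by more than the stated inputs imply, and the same happens for Aim 2.

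What is at stake is modest: whether the printed planning figures belong to the planned analyses, and whether the protocol is clear about who enters Aim 1.

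**Working it through.** **Inputs.** d = 0.2, ICC = 0.09, and N and entries as in Table 1. The counts themselves are right: 200 × 0.77 = 154; 112 × 0.76 = 85; 224 × 0.76 = 170. Alpha and sidedness are not stated for this calculation, so two-sided 0.05 is assumed. The package's internal formula is not shown, so the standard design-effect method stands in for it.

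**Method.** With m completed entries per person:

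- design effect DE = 1 + (m − 1) × 0.09
- effective sample n_eff = N × m / DE, half per group
- power ≈ Φ(0.2 × √n_eff / 2 − 1.96) = Φ(0.1 × √n_eff − 1.96)

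A noncentral-t check agrees to within 0.1 percentage point.

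**Step 1. The ideal rows.**

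- H1: DE = 1 + 111 × 0.09 = 10.99; n_eff = 200 × 112 / 10.99 = 2038; power 99.5% (printed 99%).
- H2: DE = 1 + 223 × 0.09 = 21.07; n_eff = 200 × 224 / 21.07 = 2126; power 99.6% (printed 99%, which matches if truncated).

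**Step 2. The reduced rows at their stated entries.**

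- H1: DE = 1 + 84 × 0.09 = 8.56; n_eff = 154 × 85 / 8.56 = 1529; power 97.4% (printed 93%).
- H2: DE = 1 + 169 × 0.09 = 16.21; n_eff = 154 × 170 / 16.21 = 1615; power 98.0% (printed 94%).

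Neither row reproduces.

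**Step 3. The reduced rows with the design effect left at the full entry count.**

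- H1: n_eff = 154 × 85 / 10.99 = 1191; power 93.2% (printed 93%).
- H2: n_eff = 154 × 170 / 21.07 = 1242; power 94.1% (printed 94%).

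This one rule recovers both printed figures from the listed N and entries. It counts fewer observations but keeps the clustering penalty of the complete series, so the reduced rows contradict their own entries column.

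**Step 4. Aim 1 with the right participants.** The protocol gives no phase 1 retention rate, so N is shown over a range, with 85 entries and DE = 8.56:

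| N with phase 1 data (assumed) | n_eff | Power |
|---|---|---|
| 154 | 1529 | 97.4% |
| 170 | 1688 | 98.4% |
| 180 | 1787 | 98.8% |
| 190 | 1887 | 99.1% |
| 200 | 1986 | 99.4% |

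**Step 5. The two errors separated for H1.** Starting from 93.2%, changing only N to 200 gives n_eff = 200 × 85 / 10.99 = 1547 and power 97.6%. Changing only the design effect gives 97.4%. Changing both gives 99.4%. The two faults are of about equal size.

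**The case against.** The strongest reply is that the reduced row is a bound. The table title calls it a worse case, the row above already shows 200 participants, and the corrected values lie between the two printed rows. That stands as far as consequences go: the errors are conservative. It does not rescue the row, because the text calls the same scenario realistic, and under neither label does loss after phase 1 remove phase 1 data.

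A reader might infer that Aim 1 will have exactly 200 participants, so that N is understated by 46. The protocol does not settle this. It speaks of recruiting 200 and also of 100 randomised per arm. It also requires roughly 50% EMA response during phase 1, so some loss before randomisation is expected. If 200 is the number enrolled, the Aim 1 sample lies below 200 by an unstated amount.

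A reader might also infer that phase 1 data from 46 people will be thrown away. A planning N in a power table does not define an analysis set, and the Aim 1 text describes all participants. The real ambiguity is the non-adherence paragraph: read literally, it ties phase 1 analyses to later abstinence, which conflicts with the Aim 1 text.

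Finally, the source of 93% and 94% cannot be proved. Applying the 77% a second time (154 × 0.77 = 118.6) gives 92.9% and 94.1%, so it also fits, but with an N that the table does not list. The fixed design effect could be how the package treats completion. Either way, the printed power does not follow from the listed N and entries under the standard method, and the problem covers the whole table, not Aim 1 alone.

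**Conclusion.** The point holds, at minor severity. The 154 in the H1.1-1.2 reduced row comes from a retention rate that does not apply to a phase 1 analysis, and both reduced-row powers are too low for the entries listed beside them. Corrected, Aim 1 power is about 97.4% to 99.4% for N between 154 and 200, against 93% printed. Aim 2 power is about 98.0% at N = 154 and 170 entries, against 94%. The sample size and the conclusion of adequate power are unchanged.

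These figures rest on two-sided alpha 0.05 and a design-effect approximation for a two-group mean comparison that uses every prompt. They correct the printed calculation on its own terms and say nothing about the power of the zero-inflated beta models planned for the analysis.

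**What to change.** - In the H1.1-1.2 reduced row, replace 154 with the expected number with phase 1 data: 200 if that is the number randomised, otherwise the enrolled number times the pilot's phase 1 completion rate. Say which 200 is meant. Keep 77% for Aim 2.
- Compute the design effect at the completed entries (85 and 170) in both reduced rows, restate the power, and state alpha and sidedness.
- Use one label for the reduced scenario in the text and the table title.
- Add a sentence that Aim 1 includes every participant with phase 1 EMA data regardless of later completion or abstinence, and reword the non-adherence paragraph so that it no longer conflicts with this.

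The cost is two table rows and a few sentences, with no change to design, recruitment or data collection.
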